### Objectives {7}

The specific aims of this study are:Aim 1: To refine the mobile app through focus groups (to vet app content) and usability testing (to optimize app functionality) in English- and Spanish-speaking women. Focus groups will be conducted with women who were employed prior to diagnosis or at the time of consent to the BCW study [7], and who completed (neo)adjuvant chemotherapy for breast cancer. Usability testing will be conducted in individuals who were employed prior to diagnosis and are undergoing or plan to undergo treatment for a diagnosis of cancer.Aim 2: To evaluate the effect of the mobile app on job retention after completion of adjuvant therapy for breast cancer among English- and Spanish-speaking women who were employed prior to diagnosis and plan to undergo chemotherapy.*Hypothesis:* Participants randomized to the app will have higher rates of employment four months, 1 year, and 2 years after treatment completion compared to those randomized to receive the booklet.Subaim 1: To evaluate whether the effect of the app on job retention varies by characteristics including chemotherapy regimen, symptom burden, race/ethnicity, language, and job type.Aim 3: To evaluate the effect of the mobile app on confidence in asking an employer for accommodations and on receipt of workplace accommodations during and following (neo)adjuvant therapy.*Hypothesis:* Participants randomized to the app will have greater improvements in confidence in asking an employer for accommodations and will be more likely to receive requested workplace accommodations compared to those randomized to receive the booklet.Aim 4: To evaluate the effect of the mobile app on patient efficacy in communicating with the oncology provider and self-reported symptom burden during and following adjuvant therapy.*Hypothesis:* Participants randomized to the app will have higher efficacy in communicating with the provider and lower self-reported symptom burden based on the NCI Patient Reported Outcomes Common Terminology Criteria for Adverse Events (PRO-CTCAE®) system compared to those randomized to receive the booklet.Exploratory aim 1: To evaluate the effect of the mobile app on cancer treatment adherence.

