### Outcomes {12}

The primary endpoint of the trial is self-reported employment status 4 months following the completion of treatment. This is the same primary endpoint as was used in the BCW study [7]; timing the assessment of employment status based on the end of treatment rather than the date of diagnosis provides an assessment that is comparable across participants, regardless of the timing between diagnosis and start of treatment. Depending on disease characteristics, provider recommendations, and patient preferences, participants will undergo different chemotherapy regimens with differences in cycle length and total number of cycles. They, therefore, will vary in their overall chemotherapy treatment period. Our endpoint of employment status 4 months following the completion of all treatment, consequently, has a shared interpretation across types of therapy. Two additional assessments will allow us to measure long-term employment status (1 and 2 years after completion of treatment). Patients working full-time or part-time will be considered to be working (job retained) regardless of whether they worked full-time or part-time at baseline.

Secondary study endpoints include change in self-efficacy to ask an employer for accommodations, receipt of workplace accommodations, change in perceived efficacy in patient-physician interactions (PEPPI), and symptom burden. We will ask participants about accommodations requested at baseline and at each on-treatment and post-treatment survey. Those who report asking for accommodations will also be asked to report on whether their request was granted, including whether the request was granted in full, in part, or if they were given a different accommodation instead. Symptom burden will be assessed using relevant items from the Patient-Reported Outcomes version of the Common Terminology Criteria for Adverse Events (PRO-CTCAE®). Details of these analyses are included below. These four secondary outcomes will be evaluated with respect to their relationship with the primary outcome.

The endpoint for the exploratory aim is treatment adherence based on relative dose intensity (RDI), a measure that incorporates both chemotherapy dose-reductions and treatment delays, and for which a standard exists that can be compared across chemotherapy regimens. RDI is expressed as a percent; the commonly accepted threshold below which adjuvant chemotherapy for breast cancer is less effective is 85% [43–45].

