Aim 3: To evaluate the effect of the TEAMWork App on confidence in asking an employer for accommodations and on receipt of accommodations during and after adjuvant therapy.

*Analysis:* The relationship between the app and confidence asking for accommodations at the mid-point of chemotherapy and 4 months post-treatment will be evaluated using chi-squared tests. In subset analyses, the relationship between job retention and receipt of accommodations will be evaluated among participants who asked for accommodations.

Aim 4: To evaluate the effect of the TEAMWork App on patient efficacy in communicating with the provider and self-reported symptom burden during and following adjuvant therapy.

*Analysis:* Participants randomized to receive the app are hypothesized to have higher efficacy in communicating with the provider and lower symptom burden during and after treatment than those randomized to the informational booklet. Perceived efficacy in patient-physician interactions as measured by the PEPPI score will be compared by arm using the 2-sample *t*-test [22]. For each symptom, we will compare symptom incidence and severity by study arm. To compare symptoms, we will conduct 2 sets of analyses. One will compare the rate of symptom incidence by assigned study arm at the mid- and end-of-chemotherapy-treatment time-points separately. A second analysis will report an arm comparison of whether patients who reported a symptom at the mid-treatment survey experienced an increase, decrease, or cessation of that symptom at the end of chemotherapy treatment. The main analytic tool that will be used for these analyses is the chi-squared test.

Exploratory aim 1: To evaluate the effect of the TEAMWork App on treatment adherence.

*Analysis:* We will compare treatment adherence (RDI) by receipt of the app in a Wilcoxon rank sum test.

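### Receipt of accommodations is a secondary endpoint with an app-versus-booklet hypothesis, but the Aim 3 analysis compares arms only on confidence and examines receipt only among women who asked

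*Protocol article*

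**What the plan says.** In the Protocol article, Objectives {7}, the Aim 3 hypothesis has two parts. App participants should gain more confidence in asking, and they "will be more likely to receive requested workplace accommodations compared to those randomized to receive the booklet". Outcomes {12} gives receipt the same standing as confidence: "Secondary study endpoints include change in self-efficacy to ask an employer for accommodations, receipt of workplace accommodations" head the list of four.

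Statistical methods {20a} restates Aim 3 as the effect of the app "on confidence in asking an employer for accommodations and on receipt of accommodations during and after adjuvant therapy". Two analyses follow. The first concerns "The relationship between the app and confidence asking for accommodations at the mid-point of chemotherapy and 4 months post-treatment" and uses chi-squared tests. The second is the only one that mentions receipt: "In subset analyses, the relationship between job retention and receipt of accommodations will be evaluated among participants who asked for accommodations".

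Outcomes {12} adds one further use of the secondary outcomes: "These four secondary outcomes will be evaluated with respect to their relationship with the primary outcome". The same section says that women who report a request are then asked whether it was granted in full, in part or replaced by something else, so grant data exist only for women who asked.

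For Aim 4, {20a} compares symptom incidence and severity by arm. It then adds a second analysis by arm, asking if "patients who reported a symptom at the mid-treatment survey experienced an increase, decrease, or cessation of that symptom at the end of chemotherapy treatment".

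**The concern.** The stated analysis answers a different question from the aim printed above it. Aim 3 asks whether the app changes receipt. The receipt analysis asks whether receipt goes with keeping a job. The second question is an observational association, close to what the earlier Breast Cancer and the Workforce (BCW) study already reported (Introduction {6a}). It would not show that the app did anything.

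The population is the second difficulty. Women who asked are a subset formed after randomisation, and the app teaches and models asking. If an arm comparison is added later using the only population that the plan names for receipt, the two groups of askers need not be alike, and randomisation no longer protects the contrast.

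At stake is direct randomised evidence on the employer-side step of the intended pathway, from better communication to more accommodations to job retention. If the primary result is null, this comparison would help show where the pathway failed. If it is positive, it would help show why.

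**Working it through.** **1. Is there an arm comparison of receipt anywhere?** Each place that could supply one:

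| Section | What it gives for receipt |
|---|---|
| Objectives {7} | An app-versus-booklet hypothesis |
| Outcomes {12} | Secondary endpoint; to be related to the primary outcome |
| Sample size {14}, Aim 3 | Nothing; powered on confidence only |
| Statistical methods {20a}, Aim 3 | Related to job retention among askers; arm not named |
| Additional analyses {20b} | Nothing beyond what is already described |
| Non-adherence and missing data {20c} | Analysis as randomised, but no contrast defined for receipt |

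Confidence, patient-physician efficacy and symptoms each have an explicit arm comparison in {20a}. Receipt is the only one of the four secondary endpoints without one.

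**2. The plan's own Aim 3 figure.** Sample size {14} states 80% power with 167 per arm for 30% against 45% on confidence, two-sided 5%. With d = p2 − p1 and p̄ the mean of the two rates:

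power = Φ{[d√n − 1.96√(2p̄(1−p̄))] / √(p1(1−p1) + p2(1−p2))}

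- d√n = 0.15 × √167 = 1.938
- p̄ = 0.375, so 1.96 × √0.46875 = 1.342
- denominator: √(0.21 + 0.2475) = 0.676
- Φ(0.596/0.676) = 81.1%

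This agrees with the stated 80%. The figure is sound, but it concerns confidence, not receipt.

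**3. What could an arm comparison of receipt detect?** The documents give no receipt rate and no share of women who ask, so both are assumed over a range. The same formula is used for a 15-point difference, with control rates from 30% to 60%:

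| Population | n per arm | Power |
|---|---|---|
| All evaluable women | 167 | 79% to 84% |
| Askers only, 80% ask | 134 | 69% to 75% |
| Askers only, 50% ask | 84 | 49% to 54% |
| Askers only, 30% ask | 50 | 32% to 36% |

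The rows show the cost in sample size for an equal difference. They do not imply that the true difference is the same in both populations.

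**4. Why the denominator matters (all rates assumed).** In controls, 50% ask and 70% of requests are granted. The app leaves those requests unchanged but induces extra women to ask, and 40% of the extra requests are granted.

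| App asking rate | Receipt, all women: booklet / app | Granted among askers: booklet / app |
|---|---|---|
| 50% | 35% / 35% | 70% / 70% |
| 60% | 35% / 0.35 + 0.10×0.40 = 39% | 70% / 0.39÷0.60 = 65% |
| 70% | 35% / 0.35 + 0.20×0.40 = 43% | 70% / 0.43÷0.70 = 61% |

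In the last row the app is 8 points better among all women and 9 points worse among askers. With no effect on asking, the first row, the distortion disappears.

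**5. Aim 4.** The first symptom analysis compares incidence by arm at mid-chemotherapy and at the end of chemotherapy, without restricting to women with symptoms. Only the second conditions on having the symptom at mid-treatment, which follows randomisation and is a status the app aims to change.

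**The case against.** The best defence is that a journal article condenses, and a full analysis plan may hold the test. The receipt sentence is introduced as a subset analysis, which suggests something in addition to a main comparison, and {20c} commits the main analyses to the randomised arms. This carries some weight. It does not settle the matter, because the article does write out the Aim 3 analysis, gives arm tests for the other three secondary endpoints, and says in {20b} that nothing further is planned.

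A second defence is that the hypothesis speaks of requested accommodations, so some conditioning on asking is the trial's own choice. That is fair, and the definition of receipt should respect it. The sentence still compares no arms.

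The text does not support several stronger readings that a reader might infer:

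- That Aim 3 as a whole goes untested. The confidence half has chi-squared tests by arm and its own power statement.
- That receipt will be analysed pooled over arms. The sentence does not say whether arm enters as a covariate.
- That the planned result will have the wrong sign. The reversal needs an askers-only arm comparison, which the plan does not state, and rates that are assumed here.
- That Aim 4 has the same gap. It already has arm comparisons of incidence and severity; only its second analysis is conditional.
- That the mechanism is left without any randomised test. Self-efficacy, which the Introduction makes central to the theory, is compared by arm.

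The remedy also has a cost. Counting non-askers as not having received codes women who needed nothing, who had stopped working, or who were offered help unasked as failures.

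**Conclusion.** The point holds for the receipt half of the Aim 3 hypothesis. A named secondary endpoint with a directional arm hypothesis has no stated arm comparison, and its one stated analysis uses a subset formed after randomisation and asks a different question. This rests on reading the sections against each other and needs no assumed figure. The power ranges and the asking illustration do rest on assumed rates; they show why the denominator should be fixed in advance, not what this trial will find.

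The consequence is confined to one of four secondary endpoints. The primary endpoint, its sample size and the randomisation are untouched. The conditional symptom analysis under Aim 4 is a lesser matter of labelling.

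**What to change.** Add to the Aim 3 analysis an arm comparison of the proportion of women who requested and were granted at least one accommodation, in full, in part or as an alternative. The population is all randomised women with survey data, with non-askers counted as not having received a requested accommodation and missing surveys handled as in {20c}. Adjust for site and language, the stratification factors, and name the surveys used.

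Report by arm, descriptively, the proportion who asked and the proportion granted among those who asked. The asking rate must stand beside the main result, because the composite cannot separate women who needed nothing from women who were refused. Label the receipt-retention association among askers as exploratory and non-randomised.

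For Aim 4, label the analysis among women symptomatic at mid-treatment as descriptive. Rely on end-of-chemotherapy incidence and severity in all randomised women, adjusted for baseline PRO-CTCAE.

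The cost is analysis wording only. Outcomes {12} says that requests are asked about at baseline and at every on-treatment and post-treatment survey, with the result of each request. The description of the post-treatment surveys in {18a} does not repeat this, so confirm the item is there before naming a post-treatment time point. The article reports the trial as still recruiting, so the change can be made before results are known.

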*Sample size for Aim 3:* The percent of participants who express confidence in asking an employer for accommodations will be compared by study arm. This outcome will be evaluated at the mid-point and on the last day of chemotherapy. As a conservative estimate, we expect that 80% of participants will have evaluable data at each of these time-points. Confidence in asking an employer for accommodations based on participant answers to a 5-item scale (see Data collection and management below) will be dichotomized based on the cutoff established in the observational BCW study [7]. Thirty percent of BCW study [7] participants improved their confidence in asking for accommodations between baseline and 4 months post-treatment. In the current study, with a sample size of 167 per arm, we will have 80% power to identify an improvement in confidence of 15% (e.g., 30% of control-arm participants and 45% of those who receive the app) based on a 2-sided test with a 5% type I error.

*Sample size for Aim 4:* Perceived efficacy in patient-physician interactions (PEPPI) at baseline, mid-treatment, and end of chemotherapy treatment will be compared by study arm in 3 *t*-tests. The PEPPI is a 5-item scale (with range 0–50); higher scores indicate greater self-efficacy. In a similar patient sample, the mean was 38 (standard deviation=12). Based on the retention projections described above, we expect to have data for at least *n*=167 per arm at each of the 3 time-points. For each analysis, we will be able to detect a difference from 38 to 42 (>85% power, 2-sided type I error of 5%).

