#### Post-treatment surveys

Post-treatment surveys will evaluate employment status, job changes, work hours, self-efficacy to ask for accommodations, disease status, ongoing or late effects of treatment, and financial stability. Financial worry and distress will be assessed using the 12-item Comprehensive Score for financial Toxicity (COST). Participants will complete follow-up surveys 4 months after completion of all active treatment (regardless of whether the last treatment is chemotherapy, radiation therapy, or surgery). Those who have completed chemotherapy and are receiving targeted therapy only (e.g., trastuzumab with or without pertuzumab) will be considered to have completed active treatment, as will those receiving endocrine therapy. Those who undergo neoadjuvant chemotherapy and are found to have residual disease at the time of surgery may undergo additional chemotherapy with capecitabine (Xeloda) or trastuzumab emtansine (T-DM1). Patients receiving capecitabine or trastuzumab emtansine in the post-operative setting will still be considered to have completed active treatment and will be eligible for the post-treatment survey 4 months after their completion of neoadjuvant chemotherapy, surgery, and radiation therapy (if indicated). Those who have undergone surgical resection but are awaiting reconstruction will also be considered to have completed active treatment. Additional long-term follow-up surveys will be administered 1 and 2 years after completion of active treatment. For all three follow-up surveys (those administered 4 months post-treatment completion as well as those administered 1 and 2 years later), the recall period for the PRO-CTCAE® symptom questions will be 4 weeks.

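### Aim 4 claims an effect on symptom burden during and after treatment, but both symptom comparisons the article specifies stop at the end-of-chemotherapy survey, although symptoms are collected at three later surveys

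*Protocol article*

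**What the plan says.** **Aim.** Objectives {7} states Aim 4 as the effect of the app on "patient efficacy in communicating with the oncology provider and self-reported symptom burden during and following adjuvant therapy". The Abstract lists symptom burden among the secondary outcomes with the same time frame. Under Statistical methods {20a} the aim is repeated and the hypothesis is that the app arm will have "higher efficacy in communicating with the provider and lower symptom burden during and after treatment than those randomized to the informational booklet".

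**Data.** The On-treatment surveys section places symptom assessments at about the mid-point of chemotherapy and with the last cycle. The Post-treatment surveys section adds three more, at 4 months, 1 year and 2 years after active treatment, for which "the recall period for the PRO-CTCAE® symptom questions will be 4 weeks".

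**Analysis.** Statistical methods {20a}, Aim 4, opens with a general statement that incidence and severity of each symptom will be compared by arm, then says there will be two sets of analyses. The first: "One will compare the rate of symptom incidence by assigned study arm at the mid- and end-of-chemotherapy-treatment time-points separately". The second asks whether patients with a symptom at mid-treatment "experienced an increase, decrease, or cessation of that symptom at the end of chemotherapy treatment".

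**PEPPI.** Sample size {14} says the score "at baseline, mid-treatment, and end of chemotherapy treatment will be compared by study arm in 3" t-tests. The Aim 4 analysis text names a two-sample t-test without a time-point.

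**The concern.** The aim and hypothesis cover two periods, during and after treatment. The symptom analyses cover only the first. If the article is followed as written, Aim 4 could be reported as answered from chemotherapy-period data alone. Any later comparison on the post-treatment surveys, across many symptoms and three visits, would then be chosen after the data were in hand.

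Symptom burden is a named secondary endpoint in Outcomes {12}, and the 4-month symptom assessment falls at the same survey as the primary employment endpoint. It is natural to want a randomised comparison there, and the data for it will exist.

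**Working it through.** The check is mainly a comparison of time-points.

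**1. Symptom assessments against specified arm comparisons**

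| Survey | PRO-CTCAE collected | Arm comparison specified for Aim 4 |
|---|---|---|
| Baseline | yes | none needed |
| Mid-chemotherapy | yes | incidence; start point for change |
| Last cycle | yes | incidence; end point for change |
| 4 months after treatment | yes | none |
| 1 year | yes | none |
| 2 years | yes | none |

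Post-baseline assessments: 2 + 3 = 5. Without a specified arm comparison: 3 of 5.

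**2. Is the last-cycle survey post-treatment?** Not by the article's own definitions. It is one of the on-treatment surveys. The Post-treatment surveys section counts 4 months from the end of all active treatment, whether that is chemotherapy, radiation or surgery. Intervention description {11a} notes that women on neoadjuvant chemotherapy have not yet had surgery.

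**3. Is the gap filled elsewhere?** The Aim 2 model screens symptoms occurring during the treatment period and relates them to job retention. Outcomes {12} relates the secondary outcomes to the primary outcome. Both are associations, not comparisons of symptoms by arm. Where post-treatment time-points are intended, the article names them: Aim 2 at 4 months, 1 year and 2 years, and Aim 3 confidence at 4 months.

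**4. The plan's own Aim 4 figure.** For PEPPI, with n = 167 per arm, difference 42 − 38 = 4 and SD 12:

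z = 4 / (12 × √(2/167)) − 1.96 = 3.046 − 1.96 = 1.086, so power = 0.861 (0.859 by the noncentral t).

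This agrees with the stated figure of more than 85%. The figure is right for the three time-points it covers.

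**5. What a post-treatment symptom comparison could detect (illustration).** The documents give neither symptom rates nor an expected effect. Assume a control prevalence p₁ of 30% or 50%, a reduction of 15 points to p₂, one symptom, and a two-sided 5% level without multiplicity adjustment. With p̄ the mean of p₁ and p₂:

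power = Φ{ [0.15 − 1.96 × √(2p̄(1 − p̄)/n)] / √([p₁(1 − p₁) + p₂(1 − p₂)]/n) }

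- 4 months, n = 167, 30% vs 15%: (0.15 − 1.96 × 0.0457) / 0.0450 = 1.34, power about 0.91.
- 4 months, n = 167, 50% vs 35%: (0.15 − 1.96 × 0.0541) / 0.0535 = 0.82, power about 0.79.
- 2 years, n = 210 × 0.60 = 126: about 0.82 and 0.68 respectively.

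From 30%, a 15-point reduction halves the prevalence, which is a large effect. These figures show only that the sample could detect an effect of that size in a single symptom.

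**6. Multiplicity.** With S symptoms, the incidence tests number 2S at present. Adding 4 months makes 3S; adding all three surveys makes 5S.

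**The case against.** **An SAP or the full protocol may supply the comparison, and a journal article is condensed.** This limits the claim: it can be said only that this article specifies no post-treatment symptom comparison. A reader might infer that the second half of the aim will never be tested or that the trial will yield no randomised evidence on it. The documents do not support that. The mismatch still stands, because the article is not silent: it gives the number of analyses and their time-points, and these do not match the hypothesis in the same section.

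**The general sentence on incidence and severity has no time limit.** True, and severity at a given time-point appears in neither of the two sets, so they do not fully deliver what that sentence promises. But it names no post-treatment survey either, and the text that follows ties both sets to on-treatment surveys.

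**The section on additional analyses {20b} might seem to close the list.** It does not. It says only that planned analyses will be done as described, and section {20c} then adds a mixed model over the post-treatment surveys for employment, imputation methods and app-use analyses. None of these is a comparison of symptoms, but the list is not shown to be exhaustive.

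**A reader might extend the point to PEPPI.** This is poorly supported. In the Abstract the time phrase attaches to symptom burden, not to communication efficacy. The Post-treatment surveys section does not list PEPPI, and Table 1 is not shown. Baseline, mid-treatment and end of chemotherapy form a coherent plan for it.

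**The rationale concerns symptoms during treatment.** This stands. The Introduction argues that symptom control during treatment supports working through it, and the general association with job retention says nothing specific about symptoms at 4 months. The case for a post-treatment comparison rests on the aim and hypothesis themselves, not on that rationale.

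**Conclusion.** The point holds for symptom burden. The aim, its restatement and its hypothesis include the period after treatment; symptoms are collected at three post-treatment surveys; and both specified sets of symptom analyses end at an on-treatment survey. Three of five post-baseline assessments have no specified arm comparison in this article.

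It is worth correcting, but it concerns one secondary aim. The primary analysis, sample size and randomisation are untouched, and the stated PEPPI power is reproduced. The symptom power values depend on an assumed prevalence and effect for one symptom at an unadjusted 5% level; the conclusion does not depend on them.

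**What to change.** In Statistical methods {20a}, Aim 4, do one of two things:

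- **Add the comparison.** Name an app-versus-booklet comparison of PRO-CTCAE symptom incidence and severity at the 4-month survey, adjusted for the baseline PRO-CTCAE response. Treat 1 and 2 years as supportive, and acknowledge the added multiplicity.
- **Narrow the claim.** Restrict the symptom part of Aim 4 and its hypothesis, in the Abstract, Objectives and statistical methods, to the chemotherapy period.

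The first lets the trial answer the question it poses. It needs no new data; the cost is a few more secondary comparisons. The second costs only wording, but leaves the post-treatment symptom data without a stated arm comparison.

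For PEPPI, repeat in the Aim 4 analysis the three time-points given in Sample size {14}, and word the aim so that the post-treatment period clearly refers to symptom burden. No new PEPPI collection is needed.
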